#### 2.8.3. Analysis Plan for Secondary Objectives

A.We will investigate the links between the extracted behavioural markers of apathy in real-life conditions and the self-reported measures of apathy using a linear regression. We may also compare the clusters of individuals with dementia identified based on the behavioural markers with those based on the self-reported measures of apathy (DAS subscales in particular).B.We will analyse the impact of caregiver’s perception of the dyad’s psychological status on the subsequent behavioural markers of apathy using a linear regression to show that the caregiver’s perception at day N predicts the three behavioural markers of apathy at day N + 1 (i.e., one week later) above and beyond the markers of apathy at day N.C.We also will study the relationships between the patient’s and his/her caregiver’s passive behavioural data using Granger causality test (to investigate causality between two variables in a time series) applied to the different sensor signals collected for 28 days in patient-caregiver dyads.D.We will attempt to show that passive behavioural data can predict active behavioural data collected on a daily scale. For this purpose, we will create categories derived from the active behavioural data (for instance, good–medium–bad day from the caregiver’s point of view) and use different supervised clustering methods (Linear Discriminant Analysis, Random Forest, Support Vector Machine, Artificial Neural Networks, K-Nearest Neighbours) to investigate their capacity to predict the correct category from the set of passive behavioural data.

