#### 2.1.2. Secondary Objectives

To investigate the links between the extracted behavioural markers of apathy in real-life conditions and the self-reported measures of apathyTo investigate the impact of the caregiver’s perception of the dyad’s psychological health status on the subsequent behavioural markers of apathy.To investigate the relationships between the caregiver’s and patient’s respective passive behavioural data to test the hypothesis of a dynamic causal relationship between their physiological status.To show the capacity of passive behavioural data to predict active behavioural data, as a prerequisite for the future development of a machine learning system able to automatically infer active data from passive ones after a training period.

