#### 2.6.2. Planning of Remote 28-Day Follow-Up

The remote follow-up of a couple lasts for 28 days during which partners should adopt their usual way of life. The follow-up starts at T0, on the morning of the first Monday after visit 1 and ends at T0 + 28 days, on the morning of the fourth Monday after T0 (see Figure 3). Visit 2 is scheduled as soon as possible from T0 + 28 days at the Paris Brain Institute.

As shown in Figure 3, we collect two types of data: (1) passive behavioural data from sensors, nearly continuously during the four weeks of follow-up; (2) active data from online questionnaires, once a week on a day chosen by the partner who fills the questionnaires (active behavioural data and in patient-caregiver dyads, active data on dyad’s psychological status on a daily scale) and at T0 + 28 days (in patient-caregiver dyads, dyad’s psychological status on a monthly scale).

To retain and support couples included in the study during the four weeks of follow-up, we will schedule two appointments on the phone with an investigator. These appointments will not only allow the investigator to check on the successful completion of the follow-up and to answer the couple’s questions (about technical issues for instance), but they will also provide social support for caregivers who may sometimes feel isolated. Besides, couples included in the study will have the possibility to contact an investigator on business days if needed (see the Instruction and information brochure in Supplemetary Materials, File S2). To further ensure a good quality of data collection, we will reward proper compliance with the protocol through financial compensation (€100 per couple).

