#### 2.8.2. Analysis Plan for Primary Objective

First, we will extract the metrics from both passive and active behavioural data on a monthly and a daily basis for all dyads. Using these metrics, we will explore a measurement model for the three assumed behavioural markers of apathy on the two time-scales (with monthly scale metrics for the monthly scale model and daily scale metrics for the daily scale model).

We will use Exploratory Factor Analysis (EFA) and Confirmatory Factor Analysis (CFA) in order to identify the system of metrics organised between the three markers, which is the most adapted to measure them. Statistical criteria for the validation of the measurement model tested in CFA (i.e., Root Mean Square Error of Approximation < 0.08, Standardized Root Mean Square Residual < 0.08, Comparative Fit Index > 0.9, Tucker-Lewis Index > 0.9) will guarantee its good adjustment to the data. The internal consistency of the measures of the three behavioural markers will be assessed using Cronbach’s alpha (>0.70). The reliability of the measures (on a daily scale) will also be evaluated through the correlations between the behavioural marker scores obtained on four time-steps (once a week) during the 28-day follow-up (high correlation indicating high reliability).

We will compare the measurement models and mean scores on the three behavioural markers of apathy between groups of patient-caregiver dyads and control dyads (on two time-scales). We will demonstrate that the patient-caregiver dyad’s scores on the three assumed markers of apathy can predict the dyad’s psychological state (as perceived by the spouse caregiver) using linear regression models on the monthly and daily scales. In a perspective of precision medicine, we will also investigate the disentangling of different profiles of apathy, using clustering analyses from the calculated behavioural markers of apathy.

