## 3. Expected Results and Discussion

### 3.1. Expected Results

We expect to identify a fitted measurement model for daytime activity, quality of sleep and emotional arousal from the collected passive and active data in all dyads. This will be the starting point to obtain scores for these three behavioural markers of apathy in each dyad (four scores on a daily scale and one score on a monthly scale). Scores of daytime activity, quality of sleep and emotional arousal are expected to be highly correlated and to distinguish patient-caregiver couples from healthy control couples. Besides, these scores should all contribute to predict the caregiver’s perception regarding the patient’s apathy and regarding his/her own burden and quality of life. Finally, we expect to identify different apathy profiles based on the extracted scores of daytime activity, quality of sleep, and emotional arousal. In particular, as emotional apathy has been shown to be greater in bvFTD than in AD [17,18], we should observe a profile characterized by very low emotional arousal in bvFTD.

Regarding the secondary objectives, we expect to be able to identify which behavioural marker (daytime activity, quality of sleep, or emotional arousal) best predicts the different self-reported measures of apathy. In particular, we can expect the initiation (or auto-activation) component of apathy (DAS-Initiation) to be specifically related to daytime activity whereas the emotional apathy subtype (DAS-Emotional) should be more linked with emotional arousal. Moreover, we globally expect to provide evidence of a close and reciprocal relationship between the patient’s behaviour/status and caregiver’s behaviour/status (e.g., strong causal impact between patient’s and caregiver’s physiological status assessed by sensor data). The caregiver’s state should have an impact on the subsequent measure of daytime activity, quality of sleep, and emotional arousal and reciprocally.

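### Secondary analyses B and C can be positive with no influence at work, because partners share a daily schedule (C) or dyads have stable levels (B), yet both are to be read as influence

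*Protocol article*

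**What the plan says.** Analysis C (section 2.8.3) studies the two partners' passive data "using Granger causality test (to investigate causality between two variables in a time series) applied to the different sensor signals collected for 28 days", restricted to patient-caregiver dyads. Section 2.1.2 gives its purpose as "to test the hypothesis of a dynamic causal relationship between their physiological status". Section 3.1 expects B and C together to "provide evidence of a close and reciprocal relationship", and gives a strong causal effect between the partners' sensor-measured states as its example.

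Analysis B (section 2.8.3) works by "using a linear regression to show that the caregiver’s perception at day N predicts the three behavioural markers of apathy at day N + 1". The only adjustment named is "above and beyond the markers of apathy at day N".

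Neither description mentions time of day, a dyad term, or a split between change within a dyad and differences between dyads. Section 3.2 deals with correlated residuals for the measurement model only. It does not list shared schedules or stable dyad levels as limitations of B or C.

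**The concern.** The protocol itself describes the conditions under which each method gives a positive answer without influence.

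- **C.** The couples live together (2.3.2), both partners wear sensors day and night for four weeks (2.6.2, 2.6.3), and the circadian cycle is said to govern sleep and apathy (2.1.1). One partner's recent past then carries information about the time of day, and so about the other partner's next value. A Granger test counts this as prediction.
- **B.** The daily scores are judged reliable if they agree "on four time-steps (once a week) during the 28-day follow-up (high correlation indicating high reliability", so stable dyad levels are wanted. The primary validity analysis expects markers and caregiver perception to be related across dyads (2.8.2). One earlier set of noisy scores does not fully remove the stable level. The caregiver's rating can then stand in for what is left and appear to predict the next score.

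At stake is a published statement that patients and caregivers drive each other's physiology or behaviour, when cohabitation and fixed differences between couples could produce the same result.

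**Working it through.** The protocol gives no figure for B or C. Its only computed power, 94.2% in section 2.8.1, concerns the primary model. So the check is the false-positive rate of each analysis as printed, with no influence present. Rhythm, noise and correlation values are assumptions, shown as ranges.

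**Analysis C**

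Regress y(t) on L of its own lags, then add L lags of the partner's x:

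F = [(RSS₀ − RSS₁)/L] / [RSS₁/(T − L − 1 − 2L)], rejected at 5%.

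Series length over 28 days: hourly 28 × 24 = 672; 15-minute 28 × 96 = 2,688; 5-minute 28 × 288 = 8,064.

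*Model 1:* common daily profile explaining 10–40% of variance, plus independent AR(1) noise with coefficient 0.7.

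| Epoch | False positives, as printed (all sets of runs) |
|---|---|
| 5 min | 88–100% |
| 15 min | 25–100% |
| 60 min | 5–46% |

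After subtracting each person's mean 24-hour profile the rate is 4–9%. One set used 80 simulated dyads per cell, so a rate of 30% there has a standard error of √(0.3 × 0.7/80) = 5 points.

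*Model 2:* hourly data, common 24-hour cosine of amplitude A, AR(1) noise with coefficient 0.4 and SD 1, lags 1, 2, 3 and 6, 400 runs. The cosine's share of variance is (A²/2)/(A²/2 + 1).

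| A (SD) | Share of variance | As printed | With hour-of-day terms |
|---|---|---|---|
| 0 | 0% | 4–5% | 4–6% |
| 0.25 | 3% | 5.5–8.5% | 4–6% |
| 0.5 | 11% | 22–34% | 4–6% |
| 1.0 | 33% | 97–99.5% | 4–5.5% |
| 1.5 | 53% | 100% | 4.5–5.5% |

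The two models differ at hourly epochs for a similar share of variance. The hourly result therefore depends on the rhythm's shape and the noise as well as its strength.

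Removing the profile does not remove shared irregular events. With such events at 10% of variance, 56% false positives remained at 5-minute epochs.

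**Analysis B**

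Inputs: 40 patient dyads (20 + 20) and four weekly days, giving three lagged pairs each. Marker M and rating C each equal a stable dyad level (share of variance ICC) plus daily noise. The stable levels correlate ρ between dyads, and the same-day noise of M and C correlates w. The true lagged effect is zero.

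Regressing M(n+1) on C(n) and M(n), with all variances 1, the coefficient on C converges to

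b = ICC(1 − ICC)(ρ − w) / {1 − [ICC·ρ + (1 − ICC)w]²}.

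For ICC 0.5, ρ 0.7, w 0: b = 0.25 × 0.7 / (1 − 0.35²) = 0.175/0.8775 = 0.199, which equals the simulated bias. False positives for one marker, w = 0, 2,000 runs:

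| ICC | ρ = 0.3 | ρ = 0.5 | ρ = 0.7 |
|---|---|---|---|
| 0.3 | 10% | 24% | 40% |
| 0.5 | 15% | 38% | 65% |
| 0.7 | 16% | 40% | 76% |
| 0.8 | 11% | 33% | 73% |

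With ICC = 0 or ρ = 0 the rate is 1.5–5.9%. Clustered standard errors do not help (66% against 65% at ICC 0.5, ρ 0.7), because the coefficient itself is biased.

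The protocol adjusts for the markers in the plural. At ICC 0.6, with the three stable marker levels correlated 0.8 and the markers' same-day noise correlated 0 or 0.5:

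| ρ | One marker | Three markers (noise 0 / 0.5) |
|---|---|---|
| 0.3 | 17% | 8% / 13% |
| 0.5 | 39% | 16% / 33% |
| 0.7 | 72% | 29% / 60% |

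The factor (ρ − w) shows the role of same-day variation: the bias shrinks as w nears ρ and changes sign beyond it. Runs with shared same-day variation gave 4–9%, but the formula shows that this is not general.

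**Remedies for B.** Dyad fixed effects with the lagged markers gave 3–7%, including under same-day correlation. A regression on the rating's deviation from the dyad mean, with lagged scores kept, gave 49–94% under same-day correlation. The reason is that the dyad mean contains the rating from day N + 1.

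**The case against.** The strongest reply is that this is a journal article. Epoch length, lag order, detrending and stationarity checks are commonly left to a fuller plan, and the rates for C depend heavily on them. That stands as a limit on the size of the problem. It does not remove it, because the article itself fixes the causal hypothesis, the test, the restriction to patient dyads and the expected causal conclusion.

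For B, the reply is that adjusting for three correlated markers, or same-day variation shared by marker and rating, reduces the inflation, sometimes to nominal. That also stands: over part of the plausible range B behaves well.

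The remedy for C is also open to challenge. Control couples may differ in how much time they spend together. Section 1.2 suggests that caregivers monitor the patient and give up their own activities. A patient-control difference is therefore a reference and not proof of causation.

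A reader might also infer from "once a week on a day chosen by the partner who fills the questionnaires" that the lag in B need not be one week. The documents do not support that: the phrase can mean one fixed weekday, and section 2.8.3 states the lag as one week.

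**Conclusion.** The point holds for both analyses, more firmly for C. As printed, C cannot separate influence from a shared schedule. With no influence, the false-positive rate is about 90–100% at 5-minute and 30–100% at 15-minute epochs, and from near nominal to almost 100% hourly. This rests on an assumed common daily profile and autoregressive noise.

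B can be positive with no lagged effect at roughly 4–70% (76% in the most adverse cell). This depends on ICC, between-dyad correlation, number of markers adjusted for and same-day correlation, none of which the protocol gives.

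A reader might conclude that both analyses will report influence whatever the truth. That goes too far: with a weak rhythm and hourly epochs, or with a low between-dyad correlation or a same-day correlation close to it, the rates are near nominal. Nor does B test two-way influence between partners; it tests the caregiver's perception against later markers. Both are secondary objectives, and the primary measurement model and its sample size are untouched.

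**What to change.** **C.** Subtract each person's mean 24-hour profile from the signal, or add time-of-day terms to the Granger regression. Run the identical analysis in the control dyads, who also live together and wear the same bracelets, and report it alongside as the reference. Replace causal wording in 2.1.2, 2.8.3 and 3.1 with lagged association. State shared irregular events as a remaining limitation, and say that a patient-control difference does not establish causation.

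**B.** Use a random-intercept cross-lagged model that allows same-day residual correlation between marker and rating, or dyad fixed effects together with the lagged markers. Do not use a plain regression on the rating's deviation from the dyad mean, which is itself biased when marker and rating vary together on the same day.

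**Cost.** Analysis time and wording only; all the data needed are already planned. The real downside is lower power for B, which would rest on within-dyad change over three lagged pairs per dyad.

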## 3. Expected Results and Discussion

### 3.1. Expected Results

We expect to identify a fitted measurement model for daytime activity, quality of sleep and emotional arousal from the collected passive and active data in all dyads. This will be the starting point to obtain scores for these three behavioural markers of apathy in each dyad (four scores on a daily scale and one score on a monthly scale). Scores of daytime activity, quality of sleep and emotional arousal are expected to be highly correlated and to distinguish patient-caregiver couples from healthy control couples. Besides, these scores should all contribute to predict the caregiver’s perception regarding the patient’s apathy and regarding his/her own burden and quality of life. Finally, we expect to identify different apathy profiles based on the extracted scores of daytime activity, quality of sleep, and emotional arousal. In particular, as emotional apathy has been shown to be greater in bvFTD than in AD [17,18], we should observe a profile characterized by very low emotional arousal in bvFTD.

Regarding the secondary objectives, we expect to be able to identify which behavioural marker (daytime activity, quality of sleep, or emotional arousal) best predicts the different self-reported measures of apathy. In particular, we can expect the initiation (or auto-activation) component of apathy (DAS-Initiation) to be specifically related to daytime activity whereas the emotional apathy subtype (DAS-Emotional) should be more linked with emotional arousal. Moreover, we globally expect to provide evidence of a close and reciprocal relationship between the patient’s behaviour/status and caregiver’s behaviour/status (e.g., strong causal impact between patient’s and caregiver’s physiological status assessed by sensor data). The caregiver’s state should have an impact on the subsequent measure of daytime activity, quality of sleep, and emotional arousal and reciprocally.

### 3.2. Potential Limitations of the Project

The first global limitation of the study is the risk of high dropout and poor compliance with the protocol in the recruited dyads, especially in patient-caregiver dyads who have to deal with everyday issues related to the patient’s functional difficulties. Solutions will be implemented to maintain motivation in order to limit dropout and poor compliance. Firstly, a support by phone will be offered during the follow-up (two scheduled appointments on the phone with an investigator and possibility to contact him/her if needed). This will constitute an opportunity for the investigator to warn participants in case of poor compliance (the investigator can follow data collection for each couple during follow-up thanks to a dedicated dashboard). Secondly, the financial compensation for taking part in the study will depend on proper compliance with the protocol of the whole 28-day follow-up. Besides, the protocol has been optimized to limit missing data due to poor compliance. Regarding the compliance with the wearing of the sensor bracelet, as participants are supposed to wear it nearly continuously during the follow-up, it should be less likely for them to forget it. Moreover, to avoid technical issues preventing sensor data collection, warning notifications will be sent by the smartphone application when the bracelet battery is low and as soon as the bracelet is disconnected from the app. It may be hard for some individuals with dementia to remember that they have to keep the bracelet on, but we expect that caregivers will help them with bracelet wearing. Regarding the compliance with the filling of questionnaires, notifications will be sent by the application to remind to complete them, and participants will be forced to answer all the questions to be able to send their report. Some questionnaires (those expected at T0 + 28 days) could also be completed at Visit 2 if it has not been done before. In case of missing data due to non-compliance with bracelet wearing and/or questionnaire filling during follow-up, we will try to use the available information as much as possible to contribute to the validation of measurement models on a daily and monthly scale (as long as at least 80% of the total amount of required data has been collected).

Several issues can also be discussed regarding measurement bias in the assessment of the behavioural markers of apathy from passive and active behavioural data. Measurement bias may firstly appear in passive data from sensors because they depend on many parameters that we cannot always control. In particular, measures of acceleration and GSR depend on the placement of the sensor on the body. GSR assessment has indeed been shown to differ significantly across the two halves of the upper body and traditional measures on only one side may lead to misjudgement of arousal [50]. The placement of the sensors on only one wrist in this protocol is therefore a potential issue. However, as wrist-worn devices are common, they are well accepted and individuals generally have no objection to wearing a bracelet or watch, which will increase involvement and compliance with the study [21]. Moreover, GSRs and their different phase peaks are very dependent on contextual variables that can be difficult to control. Indeed, in everyday-life conditions, it is difficult to keep a precise record of the situations in which the emotional reactions occur. This is the reason why skin conductance is generally measured under laboratory-like conditions. However, recent studies (e.g., Can et al. [51]) used GSR sensors (combined with other sensors) in real-life environments and showed that measures of skin conductance contributed to reach reliable classifications of stress level by machine learning algorithms. Regarding the active behavioural data provided by the caregiver once a week (to complete the measure of apathy markers), it is possible that the frequent monitoring of a patient’s behaviour will lead to more awareness of everyday difficulties in caregivers, thus potentially biasing their assessment of the patient’s behaviour.

Another potential measurement bias can be underlined in the assessment of behavioural markers of apathy through metrics from passive data of both individuals with dementia and their caregiver. Residual errors of prediction for the passive behavioural metrics aimed at measuring one behavioural marker will not be independent from each other and identically distributed: in particular, the residual errors relative to the caregivers’ metrics are likely to be covariates and so are the residual errors relative to the patients’ metrics. These covariances will have to be taken into account in the statistical modelling. It is also possible that the metrics extracted for both partners of one dyad are not sufficiently correlated to correspond to the measure of the same latent behavioural marker (especially for patient-caregiver dyads). If so, behavioural markers of apathy will need to be assessed using only the patient’s passive behavioural data instead of both the patient’s and caregiver’s passive behavioural data.

Finally, it seems difficult to estimate the extent of the measurement bias that might be introduced by the support provided to the caregiver through the study follow-up in an objective way. We could try to investigate a potential modification of signals from sensors worn by the caregiver between before and after a phone call with the investigator. However, we expect that this impact can be neglected (only two phone calls are scheduled with the investigator, and this is mostly for technical support).

